### Model development and validation

#### Model development

We will develop a Markov model [35] to compare outcome measures (e.g., medication adherence, symptoms, functioning, and QALYs) and costs of care in patients with schizophrenia approached with LEAN intervention plus 686 program versus 686 program alone. The model will employ Markov-type simulation of long-term health benefits, health care costs, and cost-effectiveness of the LEAN intervention. The iterative process of development of model structure and estimating model parameters will involve: reviewing of evidence-based literature, synthesizing data, consultation with health economists and statisticians, consultation with psychiatrists for expert opinion, and making some PAgs using the modified Delphi technique (Fig. 2) [36]. First-order Monte Carlo simulation [37] technique will be used to generate expected outcomes and costs of care for a hypothetical cohort of 10,000 patients.

**Fig. 2 Fig2:**
[figure not shown]
Delphi technique in model development

#### Model validation

A framework developed by McCabe et al. to test the validity of the cost-effectiveness model will be used to validate the model in this study [38]. Validity will be assessed in terms of (i) the structure of the model (descriptive validity): ensuring that the possible pathways described by the model are feasible and sensible; (ii) the inputs of the model (internal validity): justification of the data utilized in the model; (iii) the results of the model (predictive validity): comparison of the modeled estimates with those produced in real life; and (iv) the value of the model to the decision maker: comparison of the structure, inputs and results of a model with those of existing cost-effectiveness models on treatment of mental health conditions [39, 40] and justification of differences.

### Data analysis

#### Incremental cost-effectiveness ratio (ICER)

A healthcare sector perspective of the cost will be estimated using ICER and their uncertainty. The ICER will be calculated as the cost incurred to gain one QALY:
$$ ICER=\left( CT- CC\right)/\left( ET- EC\right)=\Delta C/\Delta E $$where, CT and ET are the cost and effect of a new health program i.e., LEAN intervention in this study and CC and EC are the cost and effect of the baseline comparator i.e., the community-based mental health program. Distribution of incremental costs and effects will be presented graphically on a cost-effectiveness plane, to show the estimated joint distribution of incremental costs against incremental effects. To avoid inconsistencies in the conclusions and account for the timing of events, we will apply a discounted rate of 3%; this is the rate typically used in the cost-effectiveness analysis [41].

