**Methods:**

A cost-effectiveness and cost-utility analysis of the LEAN intervention will be performed. A Markov model will be developed, validated and used to assess and compare the costs and outcomes for the LEAN intervention versus nationwide community-based mental health program. The calculated sample size is 258 participants for the analysis. A societal perspective will be applied with the time horizon of 1-year after the termination of the LEAN program. The cost-utility will be measured primarily using Quality Adjusted Life Years and the cost-effectiveness will be measured using number of relapses and number of re-hospitalizations avoided 6-month after the intervention. Univariate and probabilistic sensitivity analysis will be conducted for the analysis of uncertainty.

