A nationwide mental health program (the 686 program) was launched in China in 2005 [12] with an aim to address the challenges around the lack of integration between hospital and community health care for managing severe mental disorders. The program moved specialty mental health services into community settings providing outreach services into the community. Although the program has been able to improve access to care, it has not been able to reach its ambitious goals due to enormous challenges in the delivery of the program, greater commitment of resources, and limited available services in the community [12, 13]. Potentially, a simple, easy-to-implement and sustainable service model that can be efficient even in the presence of few mental health professionals and small mental health budgets like LEAN intervention can bring significant benefits to China’s vast population of people, not only with schizophrenia but with other kinds of severe mental disorders too. Results of the LEAN intervention showed significant improvement in medication adherence, symptoms and functioning, reduction in the risk of relapses (defined as an overall and marked increase in symptoms assessed by the health professionals through interviewing patients and family members according to the 686 Program protocol) and re-hospitalizations among patients with schizophrenia [7]; however, the study did not collect sufficient cost data and failed to analyze and report the cost-effectiveness and cost-utility of the intervention.

As a decision to adopt a new strategy or service by health policy decision-makers depends on several factors such as the ability and willingness to pay for marginal health benefits, the effectiveness of the service, and the level of need in the community. Hence, there is a need for the development of a model that can be used to estimate the cost-effectiveness and cost-utility of this novel approach that could demonstrate the added value of the program over the existing program. Hence, the objective of this study is: (i) to develop an economic model to assess the cost and health outcomes of LEAN intervention from a societal perspective and validate the model and (ii) to assess the cost-effectiveness and cost-utility of the LEAN intervention versus the 686 Program alone.

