## Methods/design

### Study design

This will be a cost-effectiveness analysis (CEA) and cost-utility analysis (CUA) of a randomized controlled trial that will compare people with schizophrenia who received the 686 Program alone (control group) with those who received the LEAN intervention along with the 686 program (intervention group) that delivered mobile phone text messaging (Table 1). CEA, the most commonly employed type of economic analysis [14] will compare the costs of averting the number of relapses and the number of re-hospitalizations in LEAN intervention as compared to the 686 program. The added value of the LEAN intervention over the 686 Program will be captured through the incremental cost-effectiveness ratio (ICER). For CUA, the effects of an intervention will be expressed as a measure of ‘utility’, commonly measured using the quality-adjusted life-year (QALY) [14]. The study will adopt a broad societal perspective on value, specifically to incorporate all health care costs such as direct medical cost of identifying individuals with schizophrenia and their medication adherence, and all health effects such as patient symptoms, functioning, relapses, and re-hospitalizations [15]. The indirect non-medical costs will include production losses related to reduced efficiency at work and absenteeism at work [16].

**Table 1 Tab1:** Types of economic analysis and economic costs of the LEAN intervention

Type of analysis	Cost category	Costs	Outcome (effect)	Results expressed as:
CEA	• Cost of human resources • Cost of intervention • Cost of using medical resources	Monetary units (CNY)	Effect of intervention (number of relapses and re-hospitalizations averted	• Cost per relapse and re-hospitalization averted • ICER
CUA	• Cost of identifying individuals with schizophrenia and their medication adherence • Cost of assessing change in symptoms and functioning	Monetary units (CNY)	Healthy lifetime gained (QALYs)	Cost per QALY gained

*CEA* Cost-effectiveness analysis, *CUA* Cost-utility analysis, *CNY* Chinese yuan, *ICER* Incremental cost-effectiveness ratio, *QALY* Quality-adjusted life-year

The disease progression model as defined by McGorry et al. [17] that states different clinical staging of psychiatric disorders has been used to develop the basic design of the model. The final framework of the Markov model will be decided after the consultation with mental health experts, public health experts, and experts in economic modeling.

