### Data

#### Cost data

The original research collected little cost data. Additional fieldwork will be conducted to supplement the cost data that will include cost data on human resources (family members and lay health supporters, and health professionals – village doctors, mental health administrators, and psychiatrists), intervention (text message development, and maintenance of texting platform and texting), project management, medication cost incurred due to increased adherence, and use of medical resources (outpatient and inpatient care), and indirect non-medical costs (efficiency at work and absenteeism at work in the past 4 weeks), assessed with the second part of the Trimbos/iMTA questionnaire for Costs associated with Psychiatric Illness (TiC-P) [21]. Primary data will be collected from the study participants by an interview and clinical data will be extracted from the medical records (Table 2).

**Table 2 Tab2:** Description of key model variables

Variables	Operational definition	Type of variable	Instrument used	Source of the data
*Demographic and epidemiologic variables*				
Population data	The initial number of people with a diagnosis of schizophrenia in each township	Continuous	Survey, records	Published literature, medical records, the 686 Program registry
Mortality rate	Incidence of death due to any reason	Continuous	Survey, records	Parent study, Medical record
Morbidity rate	Incidence of developing relapse	Continuous	Survey, records	Parent study, Medical record
Prevalence of Schizophrenia	National schizophrenia prevalence	Continuous	Survey, records	Published literature, China Health Statistical Yearbook
*Outcome variables*				
Medication adherence	The proportion of antipsychotic dosages taken over the past 30 days	Continuous	Unannounced pills count	Parent study, the 686 Program medication prescribing system
Relapse	Clinically significant exacerbation of psychotic symptoms	Dichotomous	Interview (self-report and/or caregiver report)	Parent study
Re-hospitalization	Re-hospitalization due to schizophrenia	Dichotomous	interRAI MH	Parent study, Medial record, field work
Functioning	Level of difficulty in accomplishing tasks and activities over the past 30 days	Ordinal	WHODAS 2.0	Parent study
Symptoms	Severity of psychotic symptoms	Ordinal	CGI-Sch	Parent study
*Program cost variables*				

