Intervention cost	• Cost of training in preparation for LEAN • Cost of identifying individuals with schizophrenia • Cost of assessing medication adherence • Cost of message development and management • Cost of phones • Cost of texting to patients and lay-health supporters	Continuous	Cost estimating tool	Fieldwork to be conducted as part of the study, parent study
Human resource cost	Cost of family members, lay health supporters, and health professionals (village doctors, mental health administrators, and psychiatrists)	Continuous	Cost estimating tool	Fieldwork to be conducted as part of the study
Medication cost	Antipsychotics cost incurred due to increased adherence	Continuous	Cost estimating tool	Fieldwork to be conducted as part of the study
Indirect non-medical costs: • Efficiency at work Absenteeism at work	• Number of days with reduced efficiency due to feeling ill • Number of days absent from work	Continuous	TiC-P	Fieldwork to be conducted as part of the study

Parent study is the LEAN intervention

*interRAI MH* inter Resident Assessment Instrument-Mental Health, *WHODAS* World Health Organization Disability Assessment Schedule, *CGI-Sch* Clinical Global Impression in Schizophrenia, *TiC-P* Trimbos/iMTA questionnaire for Costs associated with Psychiatric Illness

Costs will be estimated using quantities of resource used and prices. The price will be estimated using existing market prices or shadow prices (the estimated price of a good or service for which no market price exists). Costs can be fixed (that cannot be changed) or variable (flexible and changes with productivity level); the sum of both these costs will be considered as the total cost. We will develop a standardized cost collection tool and will validate it before we collect new data. For the interpretation of costs of LEAN intervention, we will estimate the incremental change to total costs.

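### The section that defines the ICER names a healthcare-sector perspective, while the abstract, objective and design name a societal one, and nothing says which is primary or which costs enter the numerator

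*Protocol article*

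**What the plan says.** Three places set a societal perspective. The abstract (Methods) states: "A societal perspective will be applied with the time horizon of 1-year after the termination of the LEAN program". Objective (i), at the end of the Background, is "to develop an economic model to assess the cost and health outcomes of LEAN intervention from a societal perspective and validate the model". The Study design section says: "The study will adopt a broad societal perspective on value".

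The planned cost items fit that perspective. Study design adds: "The indirect non-medical costs will include production losses related to reduced efficiency at work and absenteeism at work". The Cost data section lists "indirect non-medical costs (efficiency at work and absenteeism at work in the past 4 weeks" among the items for the additional fieldwork, to be measured with the TiC-P. Table 2 defines human resource cost as "Cost of family members, lay health supporters, and health professionals (village doctors, mental health administrators, and psychiatrists".

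The section on the incremental cost-effectiveness ratio opens differently: "A healthcare sector perspective of the cost will be estimated using ICER and their uncertainty". It then defines the ICER as cost per QALY gained, ΔC/ΔE. CT and CC are described only as the cost of LEAN and of the comparator programme, without a list of items.

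**The concern.** Perspective decides which costs enter ΔC. In its usual meaning, a healthcare-sector perspective leaves out production losses and the time of family and supporters that the health sector does not pay for. A societal perspective includes both. The article names one perspective for the study and another for the calculation that produces its cost-per-QALY result.

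The choice matters more here than in most evaluations. LEAN recruits lay health supporters and draws on family members to assist formal care, so the disputed items belong to the resource question itself. An analyst who followed the ICER section literally would produce a headline ratio that does not answer objective (i). The Discussion hopes both to report lower health care costs and to reduce the social cost to patient and family, so it does not settle which ratio is meant.

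**Working it through.** The article states no figure that can be reproduced, so the check is a comparison of sections followed by the algebra of the two ratios.

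**Step 1: the sections side by side**

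| Place in the protocol article | Perspective stated | Production losses | Family and lay-supporter cost |
|---|---|---|---|
| Abstract, Methods | Societal | not itemised | not itemised |
| Background, objective (i) | Societal | not itemised | not itemised |
| Study design, text | Societal | included | not itemised |
| Table 1, cost-effectiveness row | none | not listed | included, through human resources as Table 2 defines them |
| Table 1, cost-utility row | none | not listed | not listed |
| Cost data and Table 2 | none | collected | collected |
| ICER section | Healthcare sector | not itemised | not itemised |

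**Step 2: does another section reconcile them?** No. No sentence says that two perspectives will be run, or that one is the base case and the other a sensitivity analysis. Table 1 does not help. Its cost-utility row belongs to the cost-per-QALY result but lists only the cost of identifying patients and their adherence and the cost of assessing symptoms and functioning. Read literally, it fits neither perspective, because it also lacks the use of medical resources. The Study design wording is itself loose. It explains the societal view as "The study will adopt a broad societal perspective on value, specifically to incorporate all health care costs" and brings in production losses only in a later sentence.

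**Step 3: what the choice does to the ratio.** Let ΔC_H be the healthcare-sector cost difference (LEAN plus the 686 Program, minus the 686 Program alone). Let ΔP be the between-arm difference in production losses, and ΔF the between-arm difference in family and supporter time borne outside the health sector. Then

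- ΔC_S = ΔC_H + ΔP + ΔF
- ICER_S − ICER_H = (ΔP + ΔF)/ΔE

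The two ratios agree only if ΔP + ΔF = 0. The sign is not known in advance. If LEAN reduces absence from work, ΔP is negative. If it asks more time of families and supporters, ΔF is positive.

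**Step 4: size.** The article gives no wage, no hours, no programme cost and no incremental QALYs. Neither ΔP + ΔF nor ΔE can be computed from it, so no magnitude is claimed.

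**The case against.** The strongest reply is that the ICER section is loose wording, or describes a second reporting perspective, and that the objective already shows which perspective leads. Because the societal perspective appears in the abstract, the objective and the design, a later switch would be visible to readers. That weakens any worry about choosing after the results are seen. It does not remove the conflict: the one sentence that sets the perspective of the calculation would still be wrong, or would still leave the societal ICER without a place in the analysis section. Nor is this detail that an article leaves to a fuller plan, since any plan that took either perspective as its base case would contradict a statement in this article.

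Three stronger readings are tempting, and the document does not support them.

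- *That the ICER section expressly excludes family and productivity costs.* It names no excluded item. Exclusion follows only from the usual meaning of the term. Table 1 lists human resource costs, which Table 2 defines to cover family and lay supporters, for the cost-effectiveness ICER.
- *That supporters are unpaid, so a healthcare-sector ICER treats their work as free.* The article does not say they are unpaid. An award is one of the four LEAN components, and neither its content nor its recipient is described. Anything the programme pays would count under both perspectives.
- *That the disputed items could double the programme cost.* The article has no programme cost to compare with. Assumed minutes per day and an assumed wage would give gross time in the LEAN arm, whereas the ICER needs the difference between arms, and families in the control arm also give care.

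**Conclusion.** The inconsistency is real and needs correcting before the analysis. The article states a societal perspective for the study and a healthcare-sector perspective for its only defined ICER, and leaves the contents of CT and CC open. Followed as written, the ICER section would give a cost-per-QALY result that does not answer the stated objective.

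The effect on the result is (ΔP + ΔF)/ΔE. It may favour or disfavour LEAN, and its size cannot be determined from the document. The conclusion assumes only that the healthcare-sector perspective carries its usual meaning. It does not depend on whether supporters are paid.

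**What to change.** Rewrite the opening of the ICER section along these lines:

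> The base-case ICER takes the societal perspective of the study objective. CT and CC comprise all cost categories in the Cost data section and Table 2, including family and lay-supporter time and production losses.

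Align Table 1 with this, so that both rows list the same cost categories, with human resource costs and production losses included.

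If a healthcare-sector ICER is to be kept, add:

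> A healthcare-sector ICER is reported as a secondary analysis. It excludes production losses and family and supporter time that the health sector does not pay for, and retains programme payments to supporters and the cost of training.

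The last clause is needed so that the secondary ratio does not drop real programme spending along with the time costs. The societal items are already planned for collection, so no new cost category has to be added to the fieldwork. The cost is a few sentences, a corrected table and, if the secondary ICER is kept, one extra run of the model.

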#### Analysis of uncertainty

One-way sensitivity analyses will be undertaken to determine which parameters have the most impact on the results. To analyze the overall uncertainty in the model, we will employ a Probabilistic Sensitivity Analysis (PSA) in which every parameter of the model will be assigned a statistical distribution. With this technique, we will obtain the distributions of costs, health outcome values, and the resulting cost-effectiveness ratios, that will include estimation of 95% uncertainty intervals. Key input parameters to be examined will include, but will not be limited to, discount rate, intervention costs, non-adherent rates, and unit costs of schizophrenia-related morbidities. Results from the analysis will be presented in cost-effectiveness scatter plots. TreeAge Pro 2018 Software will be used as an analytical tool [42].

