**Discussion:**

If proven cost-effective, this study will contribute to the nationwide implementation of the program, not only for schizophrenia but for all kind of severe mental disorders. Markov model developed as part of the study will benefit potential researchers in analyzing cost-effectiveness of other programs. The Chinese context of the study may limit the generalizability of the study results to some extent.

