## Discussion

The purpose of this study will be to assess the cost-effectiveness and cost-utility of the LEAN intervention as compared to the nationwide community-based mental health program. With this study, we aim to investigate the cost-effectiveness and cost-utility of LEAN intervention, see an improvement in the patient’s quality of life, achieve a reduction in the relapse of cases and re-hospitalization number, achieve an increase in the medication adherence, and be able to report a decrease in the health care costs. This study will provide a novel economic model to evaluate the cost-effectiveness and cost-utility of alternative public health interventions for schizophrenia and possibly other mental disorders. Further, the model can be used in the development of mental health programs and measuring cost-effectiveness of those program in different health care settings within China and in other resource-limited countries with mental health workforce gap.

If the cost-effectiveness and cost-utility of the LEAN intervention is demonstrated, professionals might use it in the primary health care settings of China with the expectation of improving quality of life of population with schizophrenia, decreasing incidence of disease comorbidities, and reducing social costs to the patient and his/her family. Thus, the findings from our study will be of interest to clinicians and others interested in costs and outcomes of mental health services among patients with schizophrenia or other severe mental disorders.

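### The planned 95% uncertainty interval on the cost-effectiveness ratio can mislead if the probabilistic draws fall in more than one quadrant

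*Protocol article*

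**What the plan says.** The section on the incremental cost-effectiveness ratio (ICER) defines it as the cost difference divided by the effect difference between LEAN and the 686 Program: "The ICER will be calculated as the cost incurred to gain one QALY". It adds a graphical display: "Distribution of incremental costs and effects will be presented graphically on a cost-effectiveness plane".

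The section on analysis of uncertainty gives every model parameter a distribution. It then derives distributions of costs, of health outcomes and of "the resulting cost-effectiveness ratios, that will include estimation of 95% uncertainty intervals". It closes with "Results from the analysis will be presented in cost-effectiveness scatter plots".

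Two other places bear on the sign of the cost difference. The cost data section counts intervention costs and "medication cost incurred due to increased adherence" among the items to be collected. The main Discussion hopes to "be able to report a decrease in the health care costs".

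**The concern.** An interval is useful only if values further along the scale are consistently better or worse. The ICER has that property while the draws stay in one quadrant with higher cost and better outcome. It loses it when some draws show savings or a worse outcome. The same ratio can then describe opposite results, and ratios become very large in either direction as the effect difference nears zero. A reader of the 95% limits could not tell whether a negative limit means that LEAN is better and cheaper or worse and dearer.

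This matters because the abstract ties policy to the result: "If proven cost-effective, this study will contribute to the nationwide implementation of the program". An interval that mixes favourable and unfavourable draws is a poor basis for that step.

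**Working it through.** The article states no incremental cost, incremental QALY, standard error or willingness-to-pay value, so there is no figure of its own to reproduce. The check has three parts.

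**1. Algebra.** Let ΔC be incremental cost, ΔE incremental effect and λ the willingness to pay per unit of effect. The ratio is ΔC/ΔE. Net monetary benefit is NMB = λ × ΔE − ΔC, shown here at an assumed λ of CNY 50,000 per QALY.

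| ΔC (CNY) | ΔE (QALY) | ΔC/ΔE | NMB |
|---|---|---|---|
| −600 | +0.02 | −30,000 | 1,000 + 600 = +1,600 |
| +600 | −0.02 | −30,000 | −1,000 − 600 = −1,600 |
| +600 | +0.02 | +30,000 | 1,000 − 600 = +400 |
| −600 | −0.02 | +30,000 | −1,000 + 600 = −400 |

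Each pair shares a ratio and has opposite net benefit. Crossing on the cost axis alone already breaks the ordering. Saving 600 with 0.01 QALY gained gives −60,000, and saving 600 with 0.05 QALY gained gives −12,000. The second result is better but ranks higher, on the side that the ratio scale treats as worse.

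**2. Is crossing plausible here?** LEAN is delivered on top of the 686 Program, and Table 2 lists training, message development, phones, texting, human resources and extra antipsychotic cost. These push ΔC up. The hoped-for fall in health care costs pushes it down. Either sign of ΔC is therefore open on the article's own account. Nothing in the article fixes how often draws would cross.

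**3. Illustration.** The simulation took 200,000 independent normal draws of ΔC and ΔE, with percentile limits for the ratio. Every input is an assumption. NE means dearer and better, SE quadrant cheaper and better (dominant), NW dearer and worse (dominated), SW cheaper and worse.

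| Case | ΔC (SE) | ΔE (SE) | Draws by quadrant | 95% limits of ΔC/ΔE |
|---|---|---|---|---|
| A | 500 (150) | 0.03 (0.005) | NE 99.9% | 6,645 to 30,637 |
| B | 500 (500) | 0.03 (0.01) | NE 84.1%, SE 15.8%, NW 0.1% | −18,415 to 75,143 |
| C | 500 (500) | 0.02 (0.015) | NE 76.5%, SE 14.4%, NW 7.7%, SW 1.4% | −212,272 to 289,888 |

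The quadrant shares follow from the inputs. In case C, P(ΔC > 0) = Φ(500/500) = 0.841 and P(ΔE > 0) = Φ(0.02/0.015) = 0.909, so NE = 0.841 × 0.909 = 0.765.

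In case A the interval reads normally. In case C the negative ratios mix 14.4% dominant with 7.7% dominated draws, so the lower limit has no single meaning.

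Net benefit stays readable in case C. The probability that NMB exceeds zero is 0.28, 0.56, 0.78 and 0.88 at assumed λ of 10,000, 30,000, 70,000 and 210,000 CNY per QALY.

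**The case against.** The strongest reply is that the ratio interval is only one of several planned summaries. The article also plans distributions of costs and of outcomes, a cost-effectiveness plane and scatter plots. Crossing would be visible there, and dominance could be concluded without any threshold. This stands, and it limits the harm. But a plot gives no interval and no probability, and it does not repair the interval that is printed beside it.

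A second reply is that crossing may not occur, and case A shows that the interval is then sound. This also stands, so the point is conditional. The article does not say how the interval is built either. Percentile limits are assumed above, but the shared ratios in the first table do not depend on that.

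Three stronger readings are tempting and are not supported:

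- **That 258 participants make crossing certain.** The spread of PSA draws comes from the distributions given to model parameters. Effectiveness inputs are to come from published risk-prediction models, and the simulated cohort is 10,000. Trial size alone does not set that spread.
- **That the plan cannot reach a conclusion because no threshold is stated.** The Background mentions "ability and willingness to pay for marginal health benefits" only as one factor in adoption decisions, and no value is given. But a condensed article may leave a threshold or an acceptability curve to a fuller plan, and the abstract's conditional sentence is discussion, not an analysis rule.
- **That relapses and re-hospitalizations have no ratio.** The ICER section speaks only of QALYs, but Table 1 lists cost per relapse and re-hospitalization averted.

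**Conclusion.** The point holds in conditional form. The article commits to a 95% uncertainty interval on the ratio. That interval is valid only if nearly all draws lie in one quadrant with higher cost and better outcome, and the article's own expectations about cost make crossing plausible.

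The size cannot be fixed from the documents. Under the assumed inputs it runs from no problem (case A, about 6,600 to 30,600) to an interval that cannot be interpreted (case C, about −212,000 to 290,000). Those figures rest on independent normal increments chosen for illustration. The algebra needs no assumption about the trial's results. This is a worthwhile correction to a stated method. It does not show that the planned analysis as a whole is unsound.

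**What to change.** Change the analysis of uncertainty section as follows:

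- Report the ICER as the ratio of mean incremental cost to mean incremental effect, without a 95% interval on the ratio.
- Give 95% intervals for incremental cost and incremental effect separately.
- Report the share of draws in each quadrant beside the planned plane.
- Report incremental net monetary benefit, with a cost-effectiveness acceptability curve, over a range of willingness-to-pay values stated before the analysis.
- Do this per QALY and, with separate ranges, per relapse and per re-hospitalization averted.
- Base any statement that LEAN is cost-effective on net benefit.

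All of this comes from the same PSA draws. The cost is a few sentences of wording and agreement on the ranges in advance, with no new data.
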